The usability evaluation by youth will be done via a short weekly interview conducted upon arrival at the therapy session. The interview will focus on the app’s usability for the assignment given at the end of the previous session. We will assess the efficiency of the app, via ratings of the app’s learnability (how easy to figure out and remember what to do), ease of use (the time and number of steps it takes to operate, need for technical support), and error tolerance (how free of error messages, app’s ability to prevent/recover from use errors). We will also assess satisfaction with the app, via subjective ratings of its learnability (access to the assignment, memory and understanding of the lesson, motivation to practice, coaching and suggestions, self-monitoring of symptoms and changes), usability (how easy it was to use), and likeability (of specific design features). In addition, open-ended questions will be asked about: (1) where, when, and how the app was used (to understand context of use), (2) problems using the app (to identify usability problems), and (3) how the app supported homework completion (to understand the usefulness of the app). The final evaluation interview will include additional items focusing on overall experiences and impressions of the app, ratings of the app’s overall efficiency (learnability, ease of use, error tolerance), and overall satisfaction with the app (usefulness, usability, likeability). Open-ended questions will be asked about features most and least liked, facilitators and barriers to use, any negative experiences associated with the app (eg, intrusion on privacy or fear of such an intrusion), how much the app supported learning (ratings of support for access to assignments, memory and understanding of lessons, motivation, coaching and suggestions, self-monitoring, review of homework), and any suggestions for improvement.

The usability evaluation by therapists will be done via an interview following the final session, through open-ended questions about the usefulness of the app for reviewing and troubleshooting homework, whether there were any negative effects of using the app, and any suggestions for improvement.

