At pre, post, and each follow-up, treatment outcomes will be assessed. Anxiety and depression will be assessed using the same instruments as in Phase 2: the Achenbach Scales, which assess general symptomatology as reflected in internalizing problems, and externalizing problems, which often co-occur with anxiety and depression [105], the MASC-2, the CDI-2, and the ADIS. Other outcomes also will be assessed. Maladaptive cognitions will be assessed using the Children’s Automatic Thoughts Scale [106], in which youth rate the frequency over the past week of a set of 40 self-statements describing negative thoughts about physical threats, social threats, personal failure, and hostile intent. Quality of life will be assessed by the Pediatric Quality of Life Inventory [107,108], in which youth rate 23 self-statements assessing physical, emotional, social, and school functioning.

At posttreatment, a usability evaluation will be conducted with the app group (youth and therapists) following completion of the posttreatment assessment, using the same protocol as in Phase 2. To examine differences in client satisfaction between the app and no-app groups, will be assessed posttreatment (following the usability evaluation in the app group) via the Client Satisfaction Questionnaire (CSQ [109,110]), an 8-item global measure of satisfaction with service comprised of statements phrased as questions to be answered on a 4-point scale ranging from 1 (poor) to 4 (excellent). The CSQ is a well-established measure with good psychometric properties [110] that has been used in numerous studies with diverse patient samples, including children and adolescents in CBT [111,112]. Treatment fidelity will be assessed by an integrity-to-protocol checklist [113], which therapists will complete after each session. The checklist yields a proportion score reflecting the rate of adherence to the CBT treatment manual. Finally, health economic cost data will be obtained to assess cost-effectiveness of the app. Cost data will consist of technology costs, including detailed micro costing of the app program (eg, program costs, smartphone-related costs, server costs, maintenance), and the cost of time and other resources needed to integrate the app into routine clinical practice by therapists and clinics.

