##### Client Satisfaction With Service

To examine differences between the app versus no-app groups in client satisfaction, a *t*-test will be performed on total CSQ scores. Levels of satisfaction will be compared with norms established in other studies of youth in CBT treatment [111,121].

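### Client satisfaction is compared between arms, but only the app group completes the questionnaire after an interview about the app, so order and arm are fully confounded

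*Protocol article*

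**What the plan says.** The protocol article gives the CSQ a comparative purpose. Under Phase 3, Measures, it is used "To examine differences in client satisfaction between the app and no-app groups", and it is described as "an 8-item global measure of satisfaction with service".

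The same section sets its timing: satisfaction "will be assessed posttreatment (following the usability evaluation in the app group) via the Client Satisfaction Questionnaire". It also says that "a usability evaluation will be conducted with the app group (youth and therapists) following completion of the posttreatment assessment", on the Phase 2 protocol. No counterpart is described for the no-app group.

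The content of that evaluation is in Phase 2, Procedure. "The final evaluation interview will include additional items focusing on overall experiences and impressions of the app", with ratings that include "overall satisfaction with the app (usefulness, usability, likeability". "Open-ended questions will be asked about features most and least liked, facilitators and barriers to use", and also about negative experiences, support for learning and suggested improvements.

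Under Data Analysis, Client Satisfaction With Service, a t-test between the arms "will be performed on total CSQ scores", and satisfaction levels are also set against norms from other studies. Nothing in the article mentions the difference in order or allows for it.

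**The concern.** An outcome compared between randomised arms should be measured in the same way in both. Here the arms differ in what happens just before the measurement. App participants have been asked to go over what they liked, what they disliked and what went wrong with one component of their care, and they then rate the care as a whole. Controls rate it without that exercise.

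The interview could raise ratings, through attention and a chance to recall benefits, or lower them, by bringing problems to mind. Randomisation does not help, because the difference arises at measurement, after allocation. Covariate adjustment does not help either, because order does not vary within an arm.

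At stake is the reading of the satisfaction comparison. A difference could be credited to the app when the interview produced it, or a real benefit could be hidden. The app arm's comparison with outside norms has the same exposure.

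**Working it through.** **No figure to reproduce.** The article gives no sample size, SD, effect size or power for the CSQ. Its power statement (35 per group, power 0.84) concerns homework completion and has no bearing here.

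**Structure of the comparison.** Let τ be the effect of the app on satisfaction and β the effect of having just been interviewed about the app, both in SD units.

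| Arm | Usability evaluation before CSQ | Expected CSQ relative to an uninterviewed control |
|---|---|---|
| App | all participants | τ + β |
| No-app | none | 0 |

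The expected arm difference is τ + β. Indicators for arm and for order would be identical columns in any model, so only the sum can be estimated.

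**Inputs for an illustration**
- n = 50 per arm: 100 youth, 10 per group at each of 5 sites (Sample Size and Power). n = 35 per arm is shown as a lower case, being the per-group number in the power statement.
- Two-sided α = 0.05. The article states α = .05 for homework and does not give sidedness, so two-sided is assumed.
- β = 0.1, 0.2 or 0.3 SD in either direction. This range is assumed; the article gives none.

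**Formula.** For a two-sample t-test with mean shift d, df = 2n − 2 and the noncentrality is d·√(n/2). The rejection probability is P(|T| > t₀.₉₇₅,df) under that noncentral t. The smallest significant observed difference is t₀.₉₇₅,df·√(2/n).

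At n = 50, √(n/2) = 5, so shifts of 0.1, 0.2 and 0.3 SD give noncentralities of 0.5, 1.0 and 1.5. The smallest significant difference is 0.397 SD at n = 50 and 0.477 SD at n = 35.

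**Case 1: no true app effect (τ = 0), interview shifts ratings by β.** Probability of a significant result:

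| Assumed β | 50 per arm | 35 per arm |
|---|---|---|
| 0 | 5.0% | 5.0% |
| 0.1 SD | 7.9% | 7.0% |
| 0.2 SD | 16.8% | 13.1% |
| 0.3 SD | 31.8% | 23.6% |

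**Case 2: true benefit of τ = 0.5 SD (assumed), interview lowers ratings.** The net shift is 0.5 − |β|. Power:

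| Assumed reduction | Net shift | 50 per arm | 35 per arm |
|---|---|---|---|
| 0 | 0.5 SD | 69.7% | 54.1% |
| 0.1 SD | 0.4 SD | 50.8% | 37.8% |
| 0.2 SD | 0.3 SD | 31.8% | 23.6% |
| 0.3 SD | 0.2 SD | 16.8% | 13.1% |

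**With the same timing in both arms**, β = 0: the false-positive rate returns to 5%, and power for a 0.5 SD benefit at 50 per arm returns to 69.7%.

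**The case against.** The strongest reply is about weight. Client satisfaction is not part of the Phase 3 hypothesis or the listed aims, and no power calculation or decision rests on it. The size of any order effect is unknown, so the tables show only what assumed shifts would do. The CSQ concerns the service as a whole and the interview concerns the app, and the interval between them is not stated, so carry-over may be slight. Both arms also have a diagnostic interview at posttreatment, so contact with an interviewer is not in itself confined to one arm. Participants know their allocation, so a self-rating of satisfaction is open to expectation effects wherever it is placed. Finally, putting the CSQ first might colour the usability ratings.

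Most of this stands as a limit on importance. It does not remove the problem. A formal between-arm test is planned, and its design cannot separate the two explanations. The usability interview is a research evaluation held after treatment, so its effect cannot be counted as part of the app. Expectation effects would remain after reordering, but that is no reason to add an avoidable source of bias. Carry-over in the other direction would touch only app-arm usability ratings, which are not compared between arms.

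**Conclusion.** The concern holds. The timing rule is explicit, applies to one arm only and coincides completely with allocation. The CSQ comparison therefore estimates the app effect plus the effect of the interview, and cannot separate them. The direction and size of the bias cannot be taken from the document: the comparison is open to bias, not shown to be biased by a given amount. Under the assumed shifts of 0.1 to 0.3 SD, the false-positive rate at 50 per arm would be 7.9% to 31.8%. If the interview lowers ratings, power for an assumed 0.5 SD benefit would fall from 69.7% to between 50.8% and 16.8%. The consequence is confined to client satisfaction, including the app arm's comparison with norms. The homework completion analysis is untouched.

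**What to change.** Give the CSQ to both arms at the same point: with the other posttreatment measures, and before the usability evaluation in the app group. The Measures section already places that evaluation after the posttreatment assessment, so only the eight-item form moves. No participant, visit or instrument is added, and the usability evaluation is kept.

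The change must be made before posttreatment data are collected, since the confounding cannot be undone in analysis. It removes the effect of the posttreatment interview only. The Phase 2 protocol also contains short weekly interviews, so the text should say whether these are repeated in the Phase 3 app group. If they are, that difference between arms would remain and should be acknowledged when the CSQ result is reported.

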#### Study Design

We will conduct a multisite, randomized controlled pragmatic clinical trial in routine clinical settings to test the app’s effectiveness under real-world conditions in order to enhance external validity and ensure successful implementation without sacrificing scientific rigor. A pragmatic clinical trial also suits the nature of mHealth technologies, which require ongoing improvement and are subject to rapid technological change [95-97]. After pretreatment assessment, participants will be randomly assigned to receive a manualized CBT treatment either with app support (app group) or without it (no-app group). Youth assigned to CBT with the app will receive CBT treatment for 12 weeks with the app included (app group). They and their therapists will be shown how to use the app. Youth assigned to receive CBT treatment for 12 weeks with paper-based homework will be in an active control condition (no-app group). Both groups will be in treatment for 12 weeks, the typical duration of CBT. However, therapists in both the app and no-app groups will be able to provide additional sessions should they deem it clinically relevant. Duration of CBT will be recorded and group differences will be analyzed. Following the pretreatment assessment and exclusions, participants providing informed consent will be randomly assigned to treatment group. Random assignment will be done at each test site separately by the site coordinator. At each site, half the participants will be assigned to each group in order to control for site-specific variables (eg, type of CBT delivered, professional background of therapist). To assess the app’s effectiveness both immediately and over time, assessments will be done at the end of the 12-week treatment (posttreatment) and again after 6 months (follow-up 1) and 12 months (follow-up 2). At each time-point, participants will receive a CAD$30 gift card as an honorarium.

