##### Cost-Effectiveness of CBT with App Support

Cost-effectiveness will be computed for several treatment outcomes (anxiety, depression, quality of life) using the cost data described above (dollar values). An incremental cost-effectiveness ratio will be calculated for the measures at posttreatment and follow-ups 1 and 2. The analysis will use a health care sector perspective. Costs that are equal in both treatment alternatives will be excluded, because they would not impact the results. The study will use Ontario provincial list costs for health care services and market values for other resources when available. All costs will be shown in current values using the Canadian Consumer Price Index. Costs over 1 year will be discounted at a 5% discount rate and a sensitivity analysis will use 0% and 3% discount rates. We will follow Canadian Agency for Drugs and Technologies (2006) guidelines [122], the Institute of Health Economics economic evaluation report [123], and methods for costing the alternatives and performing the cost-effectiveness analysis (CEA) [124]. The cost and effectiveness outcomes will be further analyzed using economic decision modeling techniques. The modeling will include consideration of the uncertainty in both effectiveness measures and different cost variables using probabilistic sensitivity analysis techniques that allow simulation of the expected outcomes using a cost-effectiveness plane that shows the estimated incremental cost and effectiveness estimates and their mean value. Further, the results will be shown using the Cost Effectiveness Acceptability Curves, the most widely used tool to show the probability that the new technology will be accepted with different societal willingness to pay for it. The modeling part of the CEA will use state of the art modeling practices and International Society for Pharmacoeconomics and Outcomes Research good modeling guidelines [123,125,126].

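### The listed cost data cover only app technology and app integration, which does not fit the stated perspective and exclusion rule when CBT delivery may differ between arms

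*Protocol article*

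**What the plan says.** Four statements in the Phase 3 part of the protocol article bear on this.

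- **Measures** defines the cost data: "Cost data will consist of technology costs, including detailed micro costing of the app program", with examples such as program, smartphone, server and maintenance costs, and "the cost of time and other resources needed to integrate the app into routine clinical practice by therapists and clinics".
- **Cost-Effectiveness of CBT with App Support** computes cost-effectiveness "using the cost data described above (dollar values"), so it points back to that list. The ratio is to be calculated at posttreatment and at both follow-ups.
- The same section sets the frame: "The analysis will use a health care sector perspective". Its rule for leaving costs out is: "Costs that are equal in both treatment alternatives will be excluded, because they would not impact the results". It also names Ontario provincial list costs as the price source for health care services.
- **Study Design** sets 12 weeks of treatment in both groups, but "therapists in both the app and no-app groups will be able to provide additional sessions should they deem it clinically relevant". It continues: "Duration of CBT will be recorded and group differences will be analyzed". It does not link that record to the costing.

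The introduction to Phase 3 classes the cost-effectiveness work as exploratory.

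**The concern.** The cost list is stated in closed terms, and each item on it is incurred only where the app is used. Therapist time spent delivering CBT, a health care cost in both arms, is not on it. Leaving CBT delivery out would follow from the protocol's own rule if it were equal between arms. The Study Design section treats equality as an open question, since it allows discretionary extra sessions in either arm and plans to compare duration. Dropout is a second route to unequal therapy volume, and the Sample Size and Power section says it can be substantial.

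An analyst who follows the list literally could not detect a saving if the app arm needed fewer extra sessions, and would miss added therapist cost if it needed more. The ratio, the cost-effectiveness plane and the acceptability curve would then describe the price of the app and its integration, not the health care sector cost that the section says it is estimating.

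**Working it through.** The documents state no cost, session price, session count or ratio, so there is no figure of the plan's own to reproduce. The check is algebra, followed by an illustration on assumed prices.

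**Definitions**

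- *A*: app plus integration cost per youth (the items listed under Measures).
- *c*: cost of one CBT session.
- *dS*: mean CBT sessions per youth, app minus no-app.
- *dE*: difference in effect, app minus no-app.

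**Step 1: incremental cost on the listed data.** The no-app arm incurs none of the listed items, so incremental cost = *A* − 0 = *A*. This is positive and does not depend on *dS*.

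**Step 2: incremental cost with CBT delivery counted.** Incremental cost = *A* + *dS* × *c*.

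**Step 3: the difference.** The omitted term is *dS* × *c*, and the ratio is off by (*dS* × *c*) / *dE*.

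- *dS* = 0: no error.
- *dS* < 0: the listed data overstate incremental cost. Its sign is wrong once *dS* falls below −*A*/*c*.
- *dS* > 0: the listed data understate incremental cost.

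**Step 4: illustration.** Both ranges are assumptions: *A* = CAD 100 to 600 per youth, *c* = CAD 100 to 200 per session.

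- A one-session difference moves incremental cost by between 100/600 = 17% and 200/100 = 200% of *A*.
- The break-even *dS* = −*A*/*c* runs from −100/200 = −0.5 sessions to −600/100 = −6.0 sessions.
- At *A* = 300 and *c* = 150:

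| *dS* | Listed data | With CBT counted |
|---|---|---|
| −4 | +300 | 300 − 600 = −300 |
| −2 | +300 | 300 − 300 = 0 |
| 0 | +300 | 300 + 0 = +300 |
| +2 | +300 | 300 + 300 = +600 |

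The width of these ranges shows that the documents do not fix the size of the effect. They establish only the form of the omitted term.

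**Step 5: the two sections side by side.** The exclusion rule keeps any cost that differs by arm, and the perspective brings CBT delivery into scope. The cost list supplies no CBT delivery data to keep. If therapy use differs, the two sections cannot both be followed.

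**The case against.** The strongest reply is that the cost-effectiveness section, read as a whole, leaves room for session costs. It prices health care services at provincial list costs, which would have little purpose if only software and devices were counted, and its exclusion rule implies that unequal CBT costs stay in. A reader might infer from the Measures section that the analysis definitely counts app costs alone and that the ratio is therefore biased. The documents do not support that much. The plan is inconsistent rather than clearly confined to app costs, and error arises only if therapy use differs by arm. The reply does not remove the inconsistency, however: a price source is not a quantity, the listed pricing could refer only to time spent integrating the app, and the duration record is not tied to costing.

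Four further points have weight:

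- **Scope for savings is limited.** Both groups are planned for 12 weeks, and the only stated flexibility is additional sessions. Dropout aside, an average saving of two sessions would need the no-app arm to receive at least two more extra sessions per youth than the app arm. Nothing in the documents suggests a difference of that size.
- **Session data.** The article records CBT duration; it does not say that session number and length are recorded. Counts would have to be derived, for example from the integrity checklist that therapists complete after each session.
- **Condensed article.** Itemised resource quantities are commonly left to a fuller document, so their absence alone would be no finding. The point rests on what the article does state, namely what the cost data consist of.
- **Exploratory status.** The homework hypothesis, the sample size and the effectiveness analyses are untouched.

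**Conclusion.** The point holds as an inconsistency within an exploratory analysis. Following the stated cost list gives an incremental cost equal to the app and integration cost, whatever happens to therapy use. That conflicts with the health care sector perspective and with the rule of excluding only equal costs, because the design lets CBT delivery differ between arms. If mean sessions differ, incremental cost is off by *dS* × *c*, and the ratio and acceptability curve carry that error in a direction that cannot be known in advance. If they are equal, this source of error vanishes. The size is unknown: the break-even range of 0.5 to 6 fewer sessions in the app arm rests wholly on assumed unit costs. It is worth correcting before cost data are collected, since the remedy is cheap and the result is meant to inform adoption of the app.

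**What to change.** Reconcile the Measures and Cost-Effectiveness sections.

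1. In Measures, add to the cost data the CBT delivered to each youth in both arms, including additional sessions. Derive it from the recorded duration of CBT and the checklist completed after each session, and value it at the Ontario list costs already planned. If session length is needed for valuation, say how it will be obtained, because the article does not state that it is recorded.
2. In the Cost-Effectiveness section, state that CBT delivery is left out only if it is shown to be equal between arms.
3. If other health service use through follow-up 2 is not collected, describe the result as the cost of the app plus CBT delivery, not as a full health care sector cost.

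This costs a few lines of text and modest analysis work, using records the trial already plans to make. The drawback is a more variable incremental cost, which the planned probabilistic sensitivity analysis can carry.
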